### Study population

We have been enrolling patients with hypertension and HFpEF aged ≥20 years. Patients must have symptoms of HF and elevated natriuretic peptides at the screening visit: NT-proBNP ≥220 pg/ml [or B-type natriuretic peptide (BNP) ≥80 pg/ml] for patients with sinus rhythm (SR), or ≥660 pg/ml (or BNP ≥240 pg/ml) for patients with atrial fibrillation (AF). For the hypertension criteria: (1) patients' average systolic blood pressure (SBP) must be ≥140 mmHg or diastolic blood pressure ≥90 mmHg, obtained from BP measured three times on the reference arm in the sitting position at screening; (2) for those taking anti-hypertensive medications who are on stable antihypertensive dosage that has not been adjusted for 8 weeks, the SBP must be ≥110 mmHg. Patients with SBP <110 mmHg or resting HR <60 beats/min at the screening visit will be excluded. For the HFpEF criteria, we referred to the consensus recommendation of the Heart Failure Association of the European Society of Cardiology (31). LVEF should be ≥50% on echocardiography within 2 months before randomization. In addition, patients should have one or both of the following evidence of structural heart disease: (a) left atrial volume index ≥29 ml/m^2^ in patients with SR or ≥34 ml/m^2^ in patients with AF, (b) left ventricular mass index ≥115 g/m^2^ in males or ≥95 g/m^2^ in females. Patients should also have at least one indication of functional heart disease in terms of average E/e', septal and lateral e', peak tricuspid regurgitation velocity, and pulmonary artery systolic pressure. Patients will be excluded if they are taking any beta-blockers within 4 weeks prior to enrollment or if they have a contraindication to beta-blockers. Patients with severe chronic kidney disease (creatinine >2.4 mg/dl) or liver enzyme levels three times the normal upper limit will be excluded. Detailed inclusion and exclusion criteria are shown in Table 1.

**Table 1 T1:** Inclusion and exclusion criteria.

Inclusion criteria

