1. ≥20 years of age, male or female 2. Patients with an SBP of ≥140 mmHg or a DBP of ≥90 mmHg, or if taking anti-hypertensive medication, an SBP of ≥110 mmHg. 3. Current symptom(s) of HF at screening visit^a^ 4. Elevated natriuretic peptides: NT-proBNP ≥220 pg/ml (BNP ≥80 pg/ml) for patients with SR or ≥660 pg/ml (BNP ≥240 pg/ml) for patients with AF at screening visit 5. LVEF ≥50% by echocardiography within 2 months before the randomization 6. Structural heart disease evidenced by one or both of the following echocardiography findings a) LAVI ≥29 ml/m^2^ in patients with SR or ≥34 ml/m^2^ in patients with AF b) LVMI ≥115 g/m^2^ in male or ≥95 g/m^2^ in female 7. Functional heart disease evidenced by at least one of the following echocardiography findings a) Average E/e’ ≥9 b) Septal e’ <7 cm/s c) Lateral e’ <10 cm/s d) Peak tricuspid regurgitation velocity >2.8 m/s e) Pulmonary artery systolic pressure >35 mmHg
Exclusion criteria

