### Patient recruitment and randomization

Potential participants will be screened (visit 1) on an outpatient or inpatient basis (Figure 2). After a comprehensive interview, eligible participants will be asked to provide written informed consent to participate in the trial. A baseline survey of eligible participants covering demographics and cardiovascular comorbidities will be conducted by research nurses (Table 2). Then, using a web-based central randomization service (http://matrixmdr.com), eligible participants will then be randomly assigned to either the carvedilol-SR group or the placebo group in a 1:1 ratio (visit 2). The randomization block will be generated by an independent statistician unrelated to this study using the SAS randomization program.

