**Figure 2 F2:**
[figure not shown]
Study design of CARE-preserved HF. Patients will be randomized to either carvedilol-SR group or placebo groups. Carvedilol-SR, sustained-release carvedilol.

**Table 2 T2:** Standard protocol items: recommendation for interventional trials (SPIRIT) checklist.

	Study period			
	Enrolment (screening)	Allocation	Post-allocation	Close-out
Timepoint	Visit 1 (day −60–0)	Visit 2 (day 0)	Visit 2 (3 months)	Visit 3 (6 months)
Enrolment				
Eligibility screen	X			
Informed consent	X			
Allocation		X		
Interventions				
Intervention				
Control				
Assessments				
Baseline characteristics	X			
NT-proBNP	X	X		X
Echocardiography	X			X
12 lead electrocardiogram	X			
Vital signs	X	X	X	X
Secondary endpoints		X	X	X

NT-proBNP, N-terminal pro B-type natriuretic peptide.

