### Study outcomes and variables

The outcomes of this study are presented in Table 4. The primary efficacy outcome will be the time-averaged proportional change in NT-proBNP concentration from baseline through months 3 and 6. The secondary endpoints included the proportion of patients with an NT-proBNP decrease >20% from baseline through months 3 and 6, composite of all-cause mortality and all-cause hospitalization at 6 months. We will also assess changes in BP, HR, New York Heart Association (NYHA) classification, and quality of life at 6 months. Rate of BP control were under controlled will be compared between the two groups, which is defined as SBP <140 mmHg and diastolic BP <90 mmHg at 6 months. In addition, drug adherence and changes in echocardiographic parameters, including left atrial volume index, left ventricular mass index, E/e', e', pulmonary artery systolic pressure, and GLS will be assessed between the two groups. All adverse reactions and the incidence of the following adverse events of special interest during treatment will be assessed: symptomatic hypotension and bradycardia (investigator-reported).

**Table 4 T4:** Primary and secondary endpoints.

	Endpoints detail
Primary endpoint	Time-averaged proportional change in NT-proBNP concentration from baseline through months 3 and 6
Secondary endpoints	Proportion of patients with NT-proBNP decrease >20% from baseline through months 3 and 6
	Composite of all-cause mortality and all-cause hospitalization at 6 months
	Change in blood pressure and heart rate at 6 months
	Rate of blood pressure control at 6 months
	Change in NYHA classification at 6 months
	Change in quality of life assessed by visual analog scale (0–10)
	Drug adherence at 6 months
	Changes in echocardiographic parameter including LAVI, LVMI, E/e’, e’, pulmonary artery systolic pressure and GLS at 6 months

GLS, global longitudinal strain; LAVI, left atrial volume index; LVMI, left ventricular mass index; NT-proBNP, N-terminal pro B-type natriuretic peptide; NYHA, New York Heart Association.

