
### Sample size and statistical analysis

To date, no previous study has evaluated the effects of carvedilol-SR on HFpEF. Due to the absence of prior research and the pioneering nature of our intervention, a sample size calculation was not conducted at this preliminary stage. As this was a pilot study to explore the benefit of carvedilol-SR for HFpEF, we decided to enroll a total of 100 participants (50 in the carvedilol-SR group and 50 in the control group) across the three institutes, considering the duration of the study and the number of participating hospitals.

Categorical variables will be reported as frequencies (percentages), and continuous variables will be expressed as means ± standard deviations or medians with interquartile ranges. Categorical variables will be compared using Pearson's chi-square test or Fisher's exact test, and continuous variables will be compared using Student's *t*-test or the Mann–Whitney *U*-test.

Primary analysis of the proportional change in NT-proBNP concentration from baseline on a logarithmic scale will be performed using an analysis of covariance model with an adjustment for the baseline value. This will be calculated as the average of the geometric means of NT-proBNP at months 3 and 6 divided by the geometric mean of NT-proBNP at baseline in a natural logarithmic scale (i.e., ratio of geometric means) and summarized as the difference between the treatment groups in the ratio of the geometric means. Cumulative clinical-event rates will be calculated according to the Kaplan–Meier method, and the differences in clinical outcomes between the two treatment groups will be assessed using the log-rank test. Hazard ratios and associated 95% CIs will be calculated using a Cox proportional-hazards model. The incidence of adverse events will be calculated as relative risks with associated 95% CIs.

Missing values due to unevaluable samples or early study discontinuation will not be imputed. Patients with missing baseline NT-proBNP and/or missing 3 and 6 months will not be included in the primary analysis. The data will be primarily analyzed using intention-to-treat analysis, including all randomized patients. We will also perform a per-protocol analysis, which include all randomized patients who receive at least one dose of the study drug during the double-blind period and have no major protocol deviations. Safety outcomes will be analyzed in the safety set of patients who received the trial drug at least once.

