## Discussion

This randomized controlled trial will investigate the efficacy and safety of carvedilol-SR in reducing NT-proBNP levels in patients with HFpEF and hypertension. We believe that this prospective double-blind multicenter trial will be particularly helpful in evaluating the differential effects of these drugs on HFpEF according to GLS.

The effects of beta-blockers on patients with HFpEF remain controversial. The SENIORS trial sub-analysis showed a trend towards a beneficial effect of nebivolol on HF outcomes in patients with LVEF >35% (12). However, the proportion of patients with LVEF ≥50% was not high (only 15%), limiting the ability to draw conclusions about HFpEF. Recently, in a HFpEF analysis in the SwedeHF registry, β-blockers were not associated with a change in risk for HF admissions or cardiovascular deaths (17). In addition, in the largest propensity score-adjusted cohort of 435,897 patients with HF and EF ≥40%, beta-blocker use was associated with a higher risk of HF hospitalization as EF increased (18). Potential benefits were observed in patients with HF with mildly reduced EF, while potential risks were observed in patients with higher EF (particularly >60%). Although a more recent meta-analysis showed that beta-blocker therapy reduced all-cause mortality in patients with HFpEF (15), overall, the results of studies on the benefits of beta-blockers in HFpEF are inconsistent, and LVEF may be an important predictor of response to beta-blockers in HFpEF. Moreover, hypertension, atrial fibrillation, and coronary artery disease are common comorbidities that may benefit from beta-blockers in patients with HFpEF. Based on previous studies, we designed a trial of carvedilol SR in patients with HFpEF and hypertension. Considering only a few randomized clinical trials were performed and the LVEF cut-off value was different among studies (12–14), we will enroll patients with LVEF ≥50% and hypertension, regardless of atrial fibrillation or coronary artery disease.

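### The primary ANCOVA is valid, but prespecifying atrial fibrillation versus sinus rhythm at entry as a second covariate would gain a little precision at almost no cost

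*Protocol article*

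**What the plan says.** - **Primary model** (Sample size and statistical analysis): log-scale NT-proBNP, "analysis of covariance model with an adjustment for the baseline value". No second covariate is named.
- **Primary endpoint** (Study outcomes and variables): "time-averaged proportional change in NT-proBNP concentration from baseline through months 3 and 6".
- **Entry thresholds** (Table 1): "NT-proBNP ≥220 pg/ml (BNP ≥80 pg/ml) for patients with SR or ≥660 pg/ml (BNP ≥240 pg/ml) for patients with AF at screening visit".
- **AF patients are enrolled** (Discussion): patients enter "regardless of atrial fibrillation or coronary artery disease". The expected share with AF is not given.
- **Rhythm is known at entry**: the "12 lead electrocardiogram" is marked at the screening visit in Table 2, and the natriuretic peptide and left atrial volume criteria both depend on rhythm.
- **Allocation** (Patient recruitment and randomization): patients are "randomly assigned to either the carvedilol-SR group or the placebo group in a 1:1 ratio", using blocks. No stratification factor is named.
- **Size**: 100 patients, 50 per arm, chosen for feasibility. No effect size, SD or power is stated.

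**The concern.** The protocol's own criteria treat rhythm as a major determinant of the level of NT-proBNP, the biomarker behind the primary endpoint. Rhythm is available for everyone at no cost, but it appears neither in the described allocation nor in the primary model.

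A single baseline measurement does not carry the whole rhythm difference into follow-up. If the regression slope on log baseline is below 1, part of the AF shift is left in the residual. Two patients with the same baseline value, one in sinus rhythm and well above the lower threshold and one in AF and just above the higher one, would be expected to regress towards different means. A single common baseline line cannot represent that.

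At stake are some precision in a trial of 50 per arm and some exposure of the estimate to a chance imbalance in AF.

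**Working it through.** The plan has no sample size calculation to reproduce. The only figure that can be checked directly is the threshold ratio: 660/220 = 3.0 for NT-proBNP and 240/80 = 3.0 for BNP.

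**Assumptions, none of them in the documents.** AF share p = 0.2, 0.3, 0.5. The AF to sinus rhythm ratio of geometric means is 3 at baseline and follow-up, so D = ln 3 = 1.099 (borrowed from the thresholds, which are not measured means). Within-rhythm log SD s = 0.6 to 1.0, equal at both times. Correlation between baseline and the averaged follow-up value r = 0.5 to 0.8. For power only, an illustrative 20% reduction. From the plan: 50 per arm and two-sided alpha 0.05.

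**Formulas.** Let v = s² + p(1−p)D² and c = r·s² + p(1−p)D².
- Residual variance with baseline only: v − c²/v
- Residual variance with baseline and rhythm: s²(1 − r²)
- Slope on baseline when rhythm is omitted: c/v
- Shift of the log ratio from a 10-point AF imbalance: 0.10 × (1 − c/v) × D

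**Middle case (p = 0.3, s = 0.8, r = 0.7).**
- p(1−p)D² = 0.21 × 1.207 = 0.253; v = 0.640 + 0.253 = 0.893; c = 0.448 + 0.253 = 0.701
- Baseline only: 0.893 − 0.701²/0.893 = 0.343 (SD 0.585)
- With rhythm: 0.64 × 0.51 = 0.326 (SD 0.571)
- Ratio 0.952, a reduction of 4.8%, or about 5 patients in 100
- Power for a 20% reduction (normal approximation): 47.8% to 49.7%
- Slope c/v = 0.785, so the AF shift left after baseline is 0.215 × 1.099 = 0.236. A 10-point imbalance moves the log ratio by 0.0236, a factor of 1.024
- Standard error with baseline only: √(2 × 0.343/50) = 0.117, so that movement is about a fifth of one standard error

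With s = 0.9 instead, the residual variance goes from 0.430 to 0.413 at r = 0.7 (4.0%) and from 0.299 to 0.292 at r = 0.8 (2.6%).

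**Whole grid.** The variance ratio runs from 0.98 to 0.87, a reduction of about 2% to 13%. Power rises by about 0.7 to 5.8 percentage points. A 10-point imbalance moves the ratio by about 1% to 5%.

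**Chance imbalance.** With two independent binomial samples of 50, the probability that the AF shares differ by 10 points or more is 26%, 33% and 36% for true shares of 20%, 30% and 40%. At 30% the SD of the difference is √(2 × 0.3 × 0.7/50) = 9.2 points.

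**Validity check.** In 4,000 simulated trials per scenario in the middle case, type I error was 4.5% without rhythm and 4.4% with it. Under a true log ratio of ln 0.8 = −0.223, the mean estimates were −0.221 and −0.222, with power 46% and 48%.

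**The case against.** The strongest reply is that nothing here is wrong. Log-scale ANCOVA adjusted for baseline is a standard primary model for a randomized trial, and no part of the article promises adjustment for rhythm. The article condenses a fuller protocol, and further covariates or stratification factors may be set out in documents not shown. The trial describes itself as a pilot, and its limitations section already says that NT-proBNP may be influenced by confounding factors. All of this stands, and it limits the point to an optional improvement of a model that the article does state.

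Three stronger readings are tempting and are not supported:

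- **That omitting rhythm biases the result.** A reader might infer this from the threefold thresholds. Randomization makes the baseline-adjusted estimate unbiased on average, the simulation agrees, and the confidence interval already allows for chance imbalance.
- **That the protocol shows rhythm to be a strong determinant of the primary outcome.** The thresholds concern the level of NT-proBNP at entry. The outcome is proportional change, adjusted for baseline, and baseline already carries most of the rhythm difference. Omitting rhythm also raises the slope on baseline (0.785 against 0.70 in the middle case), so it absorbs more than the within-rhythm slope suggests. The documents say nothing about rhythm predicting change.
- **That centre should be added too, or the global longitudinal strain analysis changed.** No figure in the documents supports either, the blocks may already be stratified by centre, and the list of effect modifiers is introduced as non-exhaustive.

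**Conclusion.** The point holds as a low-severity efficiency gain. The primary ANCOVA is sound as it stands. Adding rhythm at entry would reduce residual variance by about 4% to 5% in the middle case, worth roughly 4 to 5 patients, and would remove the effect of an AF imbalance on the estimate. That imbalance is fairly likely, but a 10-point gap moves the ratio by only about a fifth of one standard error in the middle case.

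All sizes except the threshold ratio rest on assumed values for the AF share, the AF to sinus rhythm ratio, the SD and the correlation. The gain would differ if the true rhythm gap were not threefold, if the correlation lay outside the range, or if rhythm changed during follow-up. At the low end of the grid (2%), estimating the extra coefficient gives back about half the gain, since one of some 97 residual degrees of freedom is about 1%.

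**What to change.** Before unblinding, state that the primary ANCOVA contains treatment, log baseline NT-proBNP and rhythm at entry (AF or sinus rhythm) as fixed terms. If the analysis plan already lists rhythm, no change is needed.

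The cost is one line of text and one degree of freedom. No new data are needed, because rhythm is already determined for eligibility. The timing matters: a covariate added after unblinding would look data-driven.

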1. SBP <110 mmHg, or resting heart rate <60 beats/min at the screening visit 2. Patients who have a contra-indication to beta-blockers (including those with second-or third-degree atrioventricular block; respiratory diseases, including severe or uncontrolled asthma, chronic obstructive lung disease, allergic rhinitis or glottis edema; or severe peripheral vascular disease [Raynaud's syndrome, intermittent claudication]) 3. Patients who take any beta-blockers within 4 weeks before enrollment or who are expected to take another beta-blocker after randomization 4. Patients with a history of the following diseases - Amyloidosis, hypertrophic cardiomyopathy with left ventricular outflow tract obstruction, severe aortic or mitral valve stenosis, acute coronary syndrome within 3 months, percutaneous coronary intervention within 3 months, and recent cardiothoracic surgery within 3 months - Severe cerebrovascular events including ischemic stroke and hemorrhagic stroke within 6 months 5. Patients with significant kidney or liver disease - Creatinine >2.4 mg/dl or - Alanine transaminase or aspartate transaminase level is at least 3 times higher than the normal upper limit 6. Patients with a history of secondary hypertension or suspected secondary hypertension 7. Moderate-to-severe retinopathy (for example, retinal hemorrhage, visual disturbance, retinal microaneurysm within 6 months) 8. Patients in a clinical status that can significantly influence absorption, distribution, metabolism, and secretion of drugs for clinical trials: a. History of major gastrointestinal surgery, such as gastrectomy or gastric bypass surgery b. Inflammatory bowel disease within 12 months c. Current gastric ulcer, pancreatic function abnormality including pancreatitis, gastrointestinal/rectal bleeding which requires treatment d. Current urologic stenosis or obstruction which requires treatment 9. Chronic inflammatory diseases which require long-term use of anti-inflammatory treatment 10. Hypersensitivity to carvedilol 11. Patients with malignant disease including lymphoma and leukemia within 5 years 12. Patients who were prescribed other medication for any other clinical trials within the pre-analytical 28 days 13. Patients who are expected to have prolonged hospital stay due to other medical problems other than chronic heart failure (for example, femoral neck fracture) 14. Patients with a history of alcohol or drug abuse within the last 12 months 15. Patients with potential pregnancy or breastfeeding 16. Patients who are considered inappropriate by researchers to participate in the clinical trial

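### The one interval planned for adverse events is a relative risk, which cannot bound the excess harm of an uncommon event when no placebo patient has it; a risk difference with CI should be added

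*Protocol article*

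**What the plan says.** Under Sample size and statistical analysis the protocol article fixes the adverse-event measure in one sentence: "The incidence of adverse events will be calculated as relative risks with associated 95% CIs". The population is fixed there too: "Safety outcomes will be analyzed in the safety set of patients who received the trial drug at least once". The planned size is 100 patients, 50 per arm, chosen on feasibility grounds without a power calculation or any event rate.

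Two general sentences in the same section could also reach adverse events. One promises counts and percentages for categorical variables. The other says: "Categorical variables will be compared using Pearson's chi-square test or Fisher's exact test". Neither yields an interval for a treatment effect. The only other interval for a binary or event outcome is the hazard ratio, which belongs to the clinical outcomes.

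Study outcomes and variables singles out two investigator-reported events of special interest, symptomatic hypotension and bradycardia, alongside all adverse reactions.

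**The concern.** A pilot of a beta-blocker in this population should let the reader judge how much extra harm is compatible with the data. A ratio does this poorly when the comparator count is very small. With no placebo event the denominator is zero, so the estimate and its upper limit are infinite. With no event in either arm there is no ratio at all. The second case is informative, because it rules out a large excess, yet the planned interval would be blank.

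What is at stake is the safety summary for individual uncommon events, possibly including the two events of special interest. The efficacy analysis and the sample size do not depend on it.

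**Working it through.** **Inputs.** From the article: 50 patients per arm, the safety set of treated patients (so at most about 50 per arm), and relative risk with 95% CI. Assumed, because the article gives none: true placebo rates p of 1% to 10% for a single event type. The article states no figure here to reproduce.

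**Step 1: how often the denominator is empty.** P(no placebo event) = (1 − p)^50. P(at most one) = (1 − p)^50 + 50p(1 − p)^49.

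| Assumed p | No event, n = 50 | At most one, n = 50 | No event, n = 45 |
|---|---|---|---|
| 1% | 0.605 | 0.911 | 0.636 |
| 2% | 0.364 | 0.736 | 0.403 |
| 3% | 0.218 | 0.555 | 0.254 |
| 5% | 0.077 | 0.279 | 0.099 |
| 10% | 0.005 | 0.034 | 0.009 |

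The n = 45 column shows that modest loss from the safety set changes little.

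**Step 2: the two measures on the same counts** (carvedilol-SR versus placebo). The relative risk interval is the score (Koopman) interval. The risk difference interval is Newcombe's, built from the Wilson limits l and u of each arm: lower = d − √[(p1 − l1)² + (u2 − p2)²], upper = d + √[(u1 − p1)² + (p2 − l2)²].

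Worked case, 5/50 versus 0/50. The Wilson limits are 0.0435 to 0.2136 for 5/50 and 0 to 0.0713 for 0/50.
- Lower = 0.10 − √(0.0565² + 0.0713²) = 0.10 − 0.091 = 0.009.
- Upper = 0.10 + √(0.1136² + 0²) = 0.214.

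| Counts | Relative risk (score 95% CI) | Risk difference, points (Newcombe 95% CI) | Fisher P |
|---|---|---|---|
| 0/50 vs 0/50 | 0/0 | 0 (−7.1 to 7.1) | – |
| 4/50 vs 0/50 | not finite (1.08 to ∞) | 8 (−0.6 to 18.8) | 0.12 |
| 5/50 vs 0/50 | not finite (1.36 to ∞) | 10 (0.9 to 21.4) | 0.056 |
| 5/50 vs 1/50 | 5.0 (0.81 to 31.8) | 8 (−2.2 to 19.5) | 0.20 |

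The score interval still supplies a lower limit for the ratio when only the placebo arm is empty. The upper limit, which would bound the harm, is what is lost. The risk difference is finite in every row.

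**Step 3: does a continuity correction rescue the ratio?** Add 0.5 to each cell at 5/50 versus 0/50. The ratio is 5.5/0.5 = 11.0. The log standard error is √(1/5.5 − 1/50.5 + 1/0.5 − 1/50.5) = 1.46, giving 0.62 to 194. This is finite but of little use, and the article specifies no such correction.

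**The case against.** The strongest reply is that this is a condensed article. Zero-cell rules, interval methods and supplementary measures normally sit in an analysis plan that is not shown. A relative risk with CI is conventional, the fix keeps it, and nothing in the article excludes a risk difference. Counts per arm would let any reader compute one. Part of this stands: the absence of a zero-cell rule is not itself a fault. What remains is that the article makes a positive choice of interval measure, and at this sample size that choice cannot bound excess harm when the placebo count is zero.

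A second reply is that the trigger is hypothetical. This also stands in part. A reader might infer that hypotension and bradycardia will probably be absent on placebo. The documents do not support that. Treated hypertensives qualify at the lower limit in Table 1, "or if taking anti-hypertensive medication, an SBP of ≥110 mmHg", and the matching exclusion is only "SBP <110 mmHg, or resting heart rate <60 beats/min at the screening visit". Rate-slowing calcium antagonists and antiarrhythmics may be used with caution. These events need not be rare on placebo, and at a 10% rate the problem all but disappears.

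A reader might also infer that the whole safety analysis fails or that safety data are lost. Neither follows. For adverse events overall an empty placebo arm is improbable, and counts, percentages and a chi-square or Fisher test are still available.

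A third reply is that a second measure can bring discordant results. That is correct. At 4/50 versus 0/50 the score interval for the ratio excludes no effect while the risk difference interval does not. At 5/50 versus 0/50 the Newcombe interval excludes zero while Fisher's P is 0.056. This is a reason to declare the intervals descriptive, not a reason to omit the risk difference.

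**Conclusion.** The point holds as a minor, cheap improvement. The relative risk is the only interval the article fixes for adverse events, and with about 50 per arm it cannot bound the excess harm of an event that no placebo patient has. The chance of that for a single event type is about 61% to 8% if the placebo rate is 1% to 5%, and 0.5% at 10%. Those rates are assumptions, so how often the problem arises is uncertain. The behaviour of the ratio once the placebo count is zero is not. The conclusion is limited to uncommon individual events, possibly including symptomatic hypotension or bradycardia. It does not touch adverse events in total, the NT-proBNP analysis or the sample size.

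**What to change.** Add to the analysis plan: in the safety set, for every adverse-event comparison, report n/N per arm and the risk difference (carvedilol-SR minus placebo) with a Newcombe 95% CI. Keep the planned relative risk beside it in all cases. A score interval without an added constant suits it: give the one finite limit when only the placebo arm has no events, and mark the ratio not estimable when both arms have none. State that these safety intervals are descriptive, so that none of them is read as a test competing with Fisher's.

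Reporting both measures always, and not switching according to the counts, avoids a choice made after seeing the data.

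The cost is two or three sentences and a few lines of code, using data already collected, with no extra patients, visits or staff. The downside is one more reported measure, whose interval can disagree at the margin with the relative-risk interval and with the planned Fisher test, as the 4/50 and 5/50 examples show.
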